### Trial sample size

We aim to detect the minimal clinically important difference (MCID) over 6 months on the two primary outcomes of i) change in hip pain during walking (NRS) and ii) change in physical function (WOMAC). The MCID in OA trials is a 1.8-unit pain change [53] and 6-unit function change [42]. The sample size calculation accounts for potential clustering by physiotherapists in the *Better Hip* group. Based on our research [54], we assume a conservative between-participant standard deviation of 2 pain units and 11 function units, correlations between baseline and 6-month scores of 0.25 for pain and 0.4 for function, an intra-cluster correlation of 0.05 and 5 physiotherapists treating participants. With these parameters, we need 90 per group to achieve 80% power to detect the MCID in function at a 0.025 significance level (due to two primary outcomes). This gives > 99% power to detect the MCID in pain. Allowing for 15% attrition, we will recruit 106 people per group (in total *n* = 212).

### Data analysis plan

We will use intention-to-treat analyses. For the two primary outcomes and other secondary continuous outcomes, mean differences in change over time between groups will be estimated via separate linear mixed-effects models, with random effects for participants and physiotherapist. Models will be adjusted for baseline outcomes and BMI (> 27 kg/m^2^ and ≤ 27 kg/m^2^). Terms for time and treatment will be included, and their interaction, and results reported as mean difference in outcomes at 6 months (primary timepoint) and at 12 months between the *Better Hip* group and control group. These models provide valid inference in the presence of missing data if the data are missing at random. An analysis will be conducted using the delta-adjustment method under the pattern-mixture modelling framework in the context of multiple imputation to assess sensitivity to missingness not at random. To aid clinical interpretation, the primary outcomes will also each be dichotomised into those who do and do not achieve the MCID in improvement in pain (1.8 NRS units) and function (6 WOMAC units). Counts and percentages of participants achieving the MCID in improvement in pain and function will be reported in each treatment group at 6 and 12 months. For binary outcomes (clinically-relevant improvement, global change, participants using any oral pain medication at least once per week, participants undergoing a hip replacement procedure, willingness to have hip replacement surgery), logistic mixed-effects models will be fitted adjusted for the outcomes at baseline where able and BMI (> 27 kg/m^2^ and ≤ 27 kg/m^2^), with random effects for participant and physiotherapist, and results reported as risk ratios and risk differences at 6 months between the treatment groups. Analysis of moderation of the treatment effect by pre-specified potential moderators (baseline willingness to have surgery, BMI) on the two primary outcomes will be assessed by including interactions between moderators and the treatment group in the regression models. For all between-group comparisons, 95% confidence intervals and *p*-values will be reported. Standard diagnostic plots will be used to verify model assumptions.

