### Outcome measures

Participant-reported outcomes will be collected online via REDCap data capture platform at baseline, 6 months and 12 months. All participants who complete the 12-month re-assessment will be given a $50 gift voucher as compensation for the considerable time they have invested in the trial. An online survey for follow-up of primary and secondary outcomes will also be conducted at 2 years post randomisation. These longer-term results will be reported separately to the main trial results and will occur after analysis of the main trial data.

Primary outcomes are reliable and valid measures recommended for use in clinical trials of hip OA [41]. These will be measured at baseline, 6 and 12 months, and include i) change in average severity of hip pain on walking in the past week measured on an 11-point NRS, where 0 = “no pain” and 10 = “worst pain possible”; ii) change in physical function subscale of the Western Ontario and McMaster Universities Osteoarthritis Index (WOMAC) [42] with scores from 0 to 68, where higher scores indicate greater dysfunction. Conclusions about effectiveness will be based on the 6 month time point change in the primary outcomes.

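### The sample size uses a 0.025 level for each of the two primary outcomes, but the analysis plan prescribes 95% intervals for every comparison, primaries included, and does not carry the 0.025 forward

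*Protocol article*

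**What the plan says.** Three places in the protocol article bear on this.

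- **Trial sample size.** The calculation is set up "to detect the MCID in function at a 0.025 significance level (due to two primary outcomes"). The 0.025 is thus half of 0.05, and the stated reason is the number of primary outcomes. The section reports that "we need 90 per group to achieve 80% power to detect the MCID in function" and, for the other outcome, "This gives > 99% power to detect the MCID in pain".
- **Data analysis plan.** The reporting sentence reads "For all between-group comparisons, 95% confidence intervals" and p-values. It covers all between-group comparisons without exception, so it includes hip pain on walking and WOMAC function at 6 months. The section names no significance threshold.
- **Outcome measures.** "Conclusions about effectiveness will be based on the 6 month time point change in the primary outcomes". This names the comparisons that carry the conclusion. It does not give the level at which they are judged, or say whether one or both must succeed.

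The section on randomisation, blinding and allocation concealment adds that a separate statistical analysis plan will be written and published while the biostatisticians are blinded. That plan is not at hand.

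**The concern.** Halving alpha serves a purpose only if success on either outcome can support a claim. If both were required, 0.05 for each would already hold the false-positive rate at or below 5%. The sizing therefore implies a Bonferroni split, with each primary judged at 0.025. The interval that matches such a test is a 97.5% interval.

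The analysis section prescribes a 95% interval for the same comparisons. The trial's main results would then be shown at a level that differs from the one used to size it. For a p-value between 0.025 and 0.05 the two disagree: the interval excludes zero, but the planned level is not met. The article does not tell the reader which of the two governs. These comparisons carry the whole conclusion, and the Dissemination section links likely scale-up by the insurer to a finding of effectiveness.

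**Working it through.** **Inputs (Trial sample size section).** Level 0.025 per primary outcome; SD 11 (function) and 2 (pain); target differences 6 and 1.8; baseline to 6-month correlations 0.4 and 0.25; intra-cluster correlation 0.05; 5 physiotherapists, with clustering in the Better Hip arm only; 90 analysed per group; 15% attrition. Assumed because not stated: two-sided testing, and the correlation between the two outcomes (range 0 to 0.8).

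**Step 1. Reproduce the plan's figures.**

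- Level: 0.05 / 2 = 0.025, with critical value 2.2414.
- Design effect in the Better Hip arm: 1 + (90/5 − 1) × 0.05 = 1.85.
- Standard error without any gain from baseline adjustment: 11 × √((1.85 + 1)/90) = 1.957.
- Function power: Φ(6/1.957 − 2.2414) = Φ(0.824) = 79.5%, against the stated 80%.
- Pain power by the same formula: standard error 2 × √(2.85/90) = 0.356, and Φ(1.8/0.356 − 2.2414) = 99.8%, against the stated figure of more than 99%.
- Recruitment: 90/0.85 = 105.9, hence 106 per group.

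The stated figures are reproduced with two-sided 0.025 when the 0.4 correlation is not used to reduce the variance. If it is used, the standard error is 11 × √(1 − 0.4²) × √(2.85/90) = 1.794 and function power at 90 per group is 86.5%. Both variants are carried below, because the article does not say which was used. The choice does not affect the point about alpha.

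**Step 2. Compare the two interval levels.** The critical values are 1.960 (95%) and 2.2414 (97.5%), a ratio of 1.144.

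| Function, 90 per group | SE | 95% half-width | 97.5% half-width |
|---|---|---|---|
| 0.4 correlation used | 1.794 | 3.5 | 4.0 |
| 0.4 correlation not used | 1.957 | 3.8 | 4.4 |

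An observed function difference between the two half-widths in a row gives a 95% interval that excludes zero and a p-value above 0.025.

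**Step 3. How often that would happen.** If the true function difference is the planned 6 units, the chance of landing in the gap is the power at 0.05 minus the power at 0.025:

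- correlation used: 91.7% − 86.5% = about 5 percentage points;
- correlation not used: 86.5% − 79.5% = about 7 percentage points.

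For pain at the planned 1.8 units, without using the baseline correlation, the gap is 99.90% − 99.76%, or about 0.1 points. Under the planning assumptions the mismatch therefore matters mainly for function.

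**Step 4. Familywise error, if either interval excluding zero counted as success.** For independent outcomes this is 1 − (1 − α)². For correlated outcomes it is 1 − P(|Z₁| < c and |Z₂| < c) under a bivariate normal distribution.

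| Outcome correlation (assumed) | 0.05 each | 0.025 each |
|---|---|---|
| 0 | 1 − 0.95² = 9.75% | 1 − 0.975² = 4.94% |
| 0.3 | 9.51% | 4.84% |
| 0.5 | 9.07% | 4.65% |
| 0.7 | 8.35% | 4.30% |
| 0.8 | 7.81% | 4.02% |

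Whatever the correlation, the bound is 10% at 0.05 each and 5% at 0.025 each.

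**The case against.** The strongest reply is that the two sections do not state opposing rules. One fixes a test level and the other fixes what is reported. The only alpha in the article is 0.025, and it comes with its reason. P-values are to be reported and can be compared with 0.025 directly. A 95% estimation interval beside a test at 0.025 is a mismatch of presentation. The multiplicity procedure and the either-or-both rule are usual content of a statistical analysis plan, and the article says one will be published.

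Much of this stands. A reader might infer that the error control is lost, or that effectiveness may be declared on either outcome at 0.05. The document does not support that inference. Nowhere does it say that a primary is judged at 0.05, that significance is read from the 95% interval, or that one outcome suffices at that level. The 7.8% to 9.75% range depends on both of those unstated rules. The absence of a detailed multiplicity rule is not counted as a fault here, because that rule may sit in the separate plan.

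The reply does not remove the mismatch. On interval level the analysis section is not silent: it prescribes 95% for every between-group comparison, and for the two primaries that does not correspond to the level in the sample size. The separate plan would have to depart from that sentence or explain it.

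One other reading would make the levels agree: a one-sided 0.025 test matches a two-sided 95% interval. But the stated reason for 0.025 is the two primary outcomes, not sidedness. In the calculation that comes close to the stated 80%, a one-sided 0.025 would give 86.5% instead.

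**Conclusion.** The mismatch is real and limited. The 0.025 level appears only in the sample size section, and the blanket 95% interval corresponds to a 0.05 test for the two primary comparisons. The practical consequence falls on a primary p-value between 0.025 and 0.05. At the planned function effect that has a probability of about 5 to 7 percentage points, depending on whether the baseline correlation is used. A familywise error of 7.8% to 9.75%, instead of 4.0% to 4.9%, would follow only if either 95% interval excluding zero were taken as success.

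These figures assume two-sided tests, a normal approximation and an outcome correlation between 0 and 0.8. The estimand, model, data and sample size are not affected. The passages should be reconciled; the point does not amount to a must-fix failure of error control.

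**What to change.** Add a sentence or two to the Data analysis plan:

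- Each of the two 6-month primary comparisons is judged at two-sided 0.025, as in the sample size calculation, and effectiveness is claimed separately for each outcome that meets its level.
- These two comparisons are reported with 97.5% confidence intervals. Alternatively, keep 95% intervals, label them as unadjusted for multiplicity, and state that the p-value is judged at 0.025.
- All other comparisons keep 95% intervals.

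The separate statistical analysis plan should carry the same wording, and it should be settled before unblinding. A threshold chosen after seeing a p-value between 0.025 and 0.05 would not be credible.

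The cost is small. With 97.5% intervals, the two primary intervals become about 14% wider: for function the half-width goes from about 3.5 to 4.0 WOMAC units if the 0.4 baseline correlation is used, or from 3.8 to 4.4 if it is not. Labelling the 95% intervals instead costs no width. The numbers stay at 90 analysed and 106 recruited per group (212 in total).

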### Patient and public involvement

End-users and stakeholders were engaged in developing the research question, study methodology, and intervention components. Representatives from our partner organisations, Medibank, Coviu, the Australian Physiotherapy Association and Dietitians Australia as well as a consumer with hip OA (JM) provided input into the research question and study protocol, and were also named Associate Investigators on the grant application. The Medibank marketing team conceived the name of the program. A consumer (JM) provided feedback about the length and ease of access of the initial proposed questionnaire battery, and was also named an Associate Investigator on the grant application. Four physiotherapists provided specific input into the design of the hip strengthening exercises while two consumers participated in the filming/production of the exercise videos. Coviu provided clinician and researcher training in the use of the online consultation platform and feedback on the physiotherapist and dietitian manuals and participant resources. The ‘My Exercise Messages’ app had extensive iterative engagement during the development of the behaviour change message library and app which has been previously described [39]. A dietitian from Dietitians Australia and an endocrinologist (PS) provided input into the design of the portion plate. Consumers and clinicians provided input and feedback on the participant resources.

### Timelines

The Human Research Ethics Committee of The University of Melbourne gave ethical approval on 23rd February 2022. We prospectively registered the trial with the Australian New Zealand Clinical Trials Registry on 24th March 2022. Participant recruitment commenced in June 2022. Recruitment is expected to be completed in June 2024. The main trial is due for completion in June 2025 when all participants have completed 12-month data.

### Dissemination

Study findings will be disseminated through conference presentations and publication in peer-reviewed journals as well as via our Centre website, knowledge translation network, media and social media including a study infographic. If the Better Hip program is found to be effective, Medibank will likely scale up the program as an offering across its broad membership base, by adapting implementation plans set in place with the previous scale-up of the *Better Knee, Better Me* program. Trial e-learning modules and clinician manuals will be made freely available on FutureLearn (a digital education platform) and via our Centre website for accessible clinician professional development. Downloadable patient resources will also be made freely available for clinicians and consumers. The International Committee of Medical Journal Editors recommendations for authorship will be followed.

## Discussion

This protocol describes the background, aims and methods for a two-group, parallel design RCT aiming to evaluate the effectiveness of a 6-month telehealth-delivered, clinician-supported lifestyle management program (*Better Hip*) on the primary outcomes of change in hip pain while walking and physical function at 6 months, compared with an information-only control for people with hip OA. The effects of the program on these primary outcomes at 12 months as well as on other clinical outcomes at 6 and 12 months will also be evaluated. A range of other measures will provide insights into the safety, feasibility, acceptability of and engagement with this innovative remotely-delivered model of service delivery that focuses on core recommended hip OA treatments of education, exercise/physical activity, and for those with overweight and obesity, weight loss. A separate health economic evaluation at 12-months will inform implementation decisions while a separate survey to the main trial will follow-up participants at 2-years to determine longer-term outcomes. Such a service model has the potential to increase patient access to evidence-based lifestyle management programs.

## Data Availability

The datasets used and/or analysed during the current study will be made available from the corresponding author on reasonable request.

## Appendix 1: Home-based strengthening exercise protocol*

Minimum of 5 and maximum of 7 exercises, with progression as appropriate:

- 1 x functional / quadriceps exercise
- 1 x hip abductor exercise
- 1 x hip flexor exercise
- 1 x hip extensor exercise
- 1 x hip external **OR** 1 x hip adductor exercise
- (+ if the participant is undertaking the dietary weight loss program: 2 x UL exercises)

Once a participant is able to do the minimum of 5 exercises, up to two additional exercises may be added from the above groups.

**Table Taba:**

Muscle group	Exercise name	Starting position	Exercise instructions	Modification / progression options
Hip extensor exercises	Face-down-lying leg lift	Lie on your tummy with your hands folded under your chin.	Keep your hips flat on the floor/firm bed. Push your heel towards the ceiling, lifting your leg off the bed, and squeezing your buttocks the whole time. Hold for 2 seconds, and then lower your leg back to the starting position.	A pillow may be placed under the tummy for those who experience lower back discomfort.
	4-point-kneel leg lift	Kneel on your hands and knees. Place your hands directly under your shoulders and your knees directly under your hip. Lift your tailbone in the air a tiny, tiny bit so there is a very small curve in your back but your back is almost straight.	Keeping the tummy drawn in, slowly kick the study leg backwards, squeezing strongly through the buttocks. The knee should be kept at 90 degrees (i.e. short lever). Squeeze strongly through the buttock to get the leg in the air. Your thigh should go no further than parallel to your back. Bring leg back in, and repeat (no need to put the knee down on the ground between repetitions) **Keep your body very still**	Working with a cuff weight, resistance band or long lever.
	Bridge	Lie on your back with your knees bent and your feet flat on the floor/firm bed.	Squeeze your buttock muscles, tuck your tailbone under, and lift your hips and buttocks from the bed. Hold for 3 seconds. Slowly lower your bottom down to the floor/ bed. Keep your hips level during the exercise.	Perform the same exercise with the addition of a weight, as instructed by your physiotherapist.
	Split-leg bridge	Lie on your back with your knees bent and your feet flat on the floor/firm bed. Place your feet hip-width apart. Move your study leg slightly closer to your bottom and slightly in towards the center.	Keep your feet in the starting position. (Your study leg should be closer to your bottom and your non-study leg slightly further away). Lift your bottom. Take more weight through your study leg. Hold for 3 seconds. Then slowly lower your bottom down to floor/bed.	
	Double to single leg bridge	Lie on your back with your knees bent and your feet flat on the floor/firm bed.	1. Squeeze your buttock muscles, tuck your tailbone under and lift your hips and buttocks from the bed. 2. Keeping your hips level, lift your non-study leg off the floor/bed. Hold for 3 seconds. 3. Then place the non-study leg/foot back on the bed. 4. Slowly lower bottom back down to floor/bed	1. Progress duration of hold. OR 2. Move on to true single leg bridge as instructed below.
	Single leg bridge	Lie on your back with your knees bent and your feet flat on the floor/firm bed.	1. Lift your non-study leg off the floor/bed. Squeeze your buttock muscles and tuck your tailbone underneath you. 2. Keeping your hips level, lift your bottom and pelvis up off the bed using your study leg. 3. Hold for 3 seconds, then slowly lower bottom down to floor/bed. 4. Last of all, lower the non-study leg back to the floor/bed.	
	Hip raise	Lie on your back with your upper back supported on a step or firm couch, and your feet on the floor hip width apart.	Tighten your buttocks and push through your heels to bring your hips upward. Hold for 2 seconds, and then slowly lower your hips back to the starting position.	Progressions include adding a weight, or completing this exercise just on your study leg, as directed by your physiotherapist.
Functional / quadriceps exercises	Partial squats	Stand up tall with your legs shoulder- width apart. Turn your feet slightly outwards. Stay safe: Hold onto a table or chair for balance.	Bend at your hips and knees. Lower yourself down slightly, as if you were going to sit on a chair. Remember, when we sit down on a chair our bottom goes back behind us and down. Hold for 3 seconds. Slowly straighten back up.	
	Partial squats against wall	Gently lean your back against a wall. Keep your buttocks, back, and shoulders resting against the wall during the exercise. Step your feet away from the wall (about 30 cm) with your feet hip-width apart. Turn your feet slightly outwards and try to keep the weight on your heels.	Slowly slide down the wall. Keep your heels on the ground. Keep your knees in line with your feet, trying not to let your knees collapse inwards Stop before your knees go past your toes (or less if it is painful). Hold for 3 seconds. Push through your heels and slowly slide back up the wall.	1. Addition of resistance band around your knees/ Push your knees out against the resistance band. Try not to let them collapse in during the exercise. 2. Half-way holds: hold for 3 seconds at the halfway point of the exercise while going up and/or down.
	Split leg wall squats	Gently lean your back against a wall. Keep your buttocks, back, and shoulders resting against the wall at all times during the exercise. Step your feet away from the wall (about 30 cm) with your feet hip-width apart and your weight in the heels. Move your non-study leg a further 15 cm away from the wall. Your study leg will be slightly behind your non-study leg, and this will place more load/weight through your study leg.	Slowly slide down the wall. Take more weight through your study leg (the leg closest to the wall). Keep your heels on the ground. Keep your knees in line with your feet, trying not to let your knees collapse inwards. Stop before your knees go past your toes (or sooner if it is painful). Hold for 3 seconds, and push through your heels and slowly slide back up the wall.	
	Sit to stand	Sit on a firm, stable chair. Place the chair back against a wall for support if needed. Place your feet shoulder width apart.	Slowly stand with your hands crossed over your shoulders, or resting on your lap. Start by leaning forward bringing your nose over your toes. Keep your knees in line with your toes. As you lift up from the chair, push through the heels and straighten your legs until you are standing completely straight. Sit back down slowly.	1. Addition of resistance band around your knees (as shown at right) Push your knees out against the resistance band, trying not to let them collapse in during the exercise. 2. Half-way holds: Hold for 3 seconds at the halfway point of the exercise while going up and/or down. 3. Use a lower chair 4. Hold a weight
	Sit to stand with more weight on study leg	Sit in a firm, stable chair. Place the chair back against a wall for support if needed. Place your feet shoulder width apart. Take more weight on your study leg by either: (a) placing your good leg further forward so that your study leg is closer to you, or (b) shifting both your feet sideways so your study leg is lined up with the middle of your body.	Push through the heel of your study leg and slowly stand up from the chair without using your hands. Keep your knee in line with your foot during the exercise. Try to have more than half of your body weight on your study leg throughout the entire exercise Slowly return to sitting.	
	Step ups	Stand in front of a stair or step. Stay safe: Use a handrail or other hand support for balance if required.	Place your study leg up onto the step. When you are stable, push through your heel/ foot and bring up your other leg. Lightly touch your non-study leg onto the step, and step it back down slowly to the start position. Your weight should be on your study leg throughout the entire exercise. Concentrate on keeping your knee positioned over your foot throughout.	1. Use a higher step. 2. Hold on to a weight.
	Backward step downs	Stand on a step with your study leg close to the edge of the step. Stay safe: Use a handrail or other hand support for balance if required.	Bending your study leg slowly, sit your buttocks back and lean forward slightly. Make sure the knee on the study leg side is not bending/drifting in towards the midline. Lightly touch the foot of the non-study leg to the ground and then push back up to the starting position.	1. Use a higher step. 2. Hold on to a weight. 3. Use a cuff weight on the non-study leg
	Lunges	Stand with your feet shoulder-width apart and your arms either by your side or resting on your hips.	Take a large step forward with your study leg, then lower your hips down, bending your hips and knees to about 90 degrees. Keep your upper body upright, and don’t let the knee that’s forward drift inwards towards the midline. Push back up and step back to return to the starting position.	Hold weights at your sides.
	Inner-range quads over roll	Lie on a mat on the floor or on a firm bed. Put a rolled up towel under your study leg knee. Your knee will be slightly bent. Keep the knee cap and toes pointing toward the roof.	Keeping the back of the knee in contact with the towel, push the back of your knee down into the towel and straighten your study leg and SLOWLY lift the heel off the surface over 2 seconds. Hold leg as straight as it will go for 5 seconds then SLOWLY lower down over 2 seconds.	
	Seated knee extension	Sit in a firm chair (one that is higher if possible).	Slowly lift your foot up and straighten the knee until it is fully straight. Keep the back of your thigh on the chair. Hold for 5 seconds and lower slowly. *“Slowly up, hold, 2, 3, 4, 5, slowly down”.*	Tie your resistance band into a loop. Place the looped resistance band around the back leg of a chair. Sit on the chair and put your leg into the loop with the band around the front of your foot. Change colour of resistance band – red through to black. Progressions also include adding an ankle cuff weight (as guided by your physiotherapist).
Hip abductor exercises	Standing side leg raises	Face forwards and keep your back straight. Loop your resistance band around your ankles. Stay safe: Use the back of a chair or a wall for balance.	Stand tall, keeping your back straight. Try not to tilt to the side. Don’t twist as this will mean the wrong muscles are being exercised. Keep your knees straight and your toes pointing forward. Squeeze through your buttock and leg and lift your study leg out a small way to the side, leading with the heel. Hold for 1–3 seconds and then lower slowly.	Alternate option: Use an ankle cuff weight instead of resistance band. Easier option (as guided by your physiotherapist): you may do this same exercise without the use of the resistance band.
	Standing leg wall press	Stand sideways with your non-study leg against a sturdy wall.	Stand tall, tummy and bottom in. Lift the non-study leg off the floor so that your hip, thigh and knee are touching the wall. Keeping your body still, push your non-study leg into the wall. Hold for 3–5 seconds, or as directed by your physiotherapist. Return your foot to the floor and rest for a few seconds.	
	Standing leg wall press with knee bend	Stand sideways with your non-study leg against a sturdy wall.	Stand tall, tummy and bottom in. Lift the non-study leg off the floor so that your hip, thigh and knee are touching the wall. Keeping your body still, push your non- study leg into the wall. While continuing to push into the wall, slowly bend your study leg to a maximum of 45 degrees. Concentrate on keeping your knee positioned over your foot throughout. Straighten your knee and return your foot to the floor and rest for a few seconds.	
	Side-lying leg raises	Lie on your side on a firm surface, with your study leg on top. You may bend the bottom leg and use your arms for support. The body and hips should be rolled forwards, about a 1/4 turn forwards. This step is important; you should feel that you are rolling forwards slightly. This position of the body and hips should be maintained throughout the entire exercise.	Think about a strong still body and drawing your leg into the hip socket. Slowly raise the top (study) leg up, keeping your knee facing forwards. Make sure your body does not roll backwards during the exercise. Hold for 1–3 seconds, then lower down slowly.	Advanced option (As guided by your physiotherapist) Addition of the cuff weight to the leg.
	Crab walking	Place a resistance band around your thigh/knee level (easier) or around your ankles (harder) so that there is tension when your legs are separated about 10 cm. Slightly bend both knees. Stay safe: You should stand facing a table, a kitchen bench or a wall that you can reach if you lose balance.	Step sideways against the tension of the resistance band, keeping your legs apart. Do not twist or turn your body and legs. Your feet should point forwards while you are stepping sideways. Concentrate on keeping your knee positioned over your foot throughout the exercise. Take 3 steps to the left, and then 3 steps to the right. Continue for 30 seconds to complete 1 round.	Advanced options: 1. Zig-zags 2. Change resistance band colour
	Hip hitch	Stand side-on on a step, with your study leg on the step and the non-study leg hanging off the step. Stay safe: hold onto a wall or handrail.	Bend the knee on the study leg very slightly. Lower the leg that is hanging off the step by lowering that side of the pelvis down towards the floor. Push back up through the study hip to the starting position.	Using a cuff weight on the non-study leg.
	Bridge with outward leg press	Lie on your back with your knees bent and your feet flat on the floor / firm bed. Put a resistance band around your legs just above your knees as shown.	Squeeze your buttock muscles, tuck your tailbone under and lift your hips and buttocks from the floor / bed. Push your legs out against the resistance of the resistance band, holding for 1 second. Then bring your legs slowly back together and lower your buttocks down to the floor / bed.	Advanced options: 1. Change to a harder resistance band colour. 2. Push out against the resistance band more than once while the buttocks are lifted.
Hip flexor exercises	Crook lying hip bends	Lay on a firm surface/bed, with both knees bent and feet resting flat on the bed.	Think about drawing your leg up into the hip joint and slowly raise your study leg into the air. Slowly lower your study leg down. This exercise should be slow and controlled. You are aiming to work the muscles deep in the front of the hip.	Advanced Options: 1. Addition of cuff weight to the study leg, just above the knee. 2. Straighten the knee (long lever lifts)
	Face up lying hip bends off edge of bed	Lay on a firm surface/bed, with your study leg hanging off the end of the bed. Bring the knee of your non-study leg to your chest, and secure with your arms Stay safe: It is very important you make sure you tuck your tail under and keep your back flat against the bed. You should only feel this exercise in your hip/front of your thigh, not in your back at all. It may also work your stomach muscles a little.	Tuck your tail under, making sure your back is flat against the bed. Think about sucking in the leg into the hip joint, and slowly raise your study leg into the air. Keep the knee bent on your study leg. Slowly lower your study leg down towards the level of the bed but no further.	Advanced options: 1. Add a cuff weight to the study leg, just above the knee. Straightening the knee of the study leg (long lever).
	Standing knee raises	Stand tall with your legs shoulder width apart. Stay safe: Use a chair or table for balance.	Standing tall and strong, bend your study leg up so that your thigh is parallel to the ground (or lower if discomfort is experienced). Slowly lower your leg back down. Lightly touch your foot to the ground before repeating straight away. The aim of this exercise is to progressively build speed, while keeping all the movement at the hip joint. Your body (trunk and pelvis) should not be rocking backwards or forwards during the exercise.	Progressions include adding an ankle cuff weight or resistance band.
Hip adductor exercises	Crook lying leg squeeze	Lay on a firm surface with your knees bent. Keep you tour tail tucked under so your back is comfortably flat against the bed/floor. Keep your heels on the floor/bed. Place a magic circle, ball, cushion or other appropriate equipment between the knees.	You are aiming to start to work the muscles on the inside of your thighs. Gently squeeze your knees together and build up to a moderate pressure. Hold for 5 seconds, or as directed by your physiotherapist.	
	Standing resistance band adduction	Tie the resistance band to a stable support and loop it around your ankle as shown. Step away from the support to create some tension in the resistance band. The non-study leg will stay still during the exercise. Stand up straight. Keep your body facing forwards (at right angles to the band) throughout the exercise. Stay safe: use a chair or table for balance as required.	Standing tall and keeping your belly drawn in, slowly move your study leg to your midline pulling against the resistance band. Keep all your body weight supported on your non-study leg. Slowly return your study leg to the starting position.	
	Side lying hip adduction	Lie on your side on your study hip with a small rolled up towel between your rib cage and waist. Place your non-study foot in front of your knee so it is out of the way of / not on top of your study leg. (If too difficult, just lie with legs one on top of the other). Your study leg will be straight, toes pulled up towards you, knee facing forwards.	Keeping your body very still, think about sucking your thigh/leg up into the hip joint socket and slowly lift the study leg up off the bed. Keep your knee straight. This is a very small movement and there is no need to overdo it - you are aiming to simply get your foot off the ground. You should feel the work in your inner thigh of the study leg. Slow controlled lift up, slow controlled lower down.	Progressions include adding an ankle cuff weight.
	Crook lying resistance band adduction	Lie on your back with your knees bent and your feet flat on the floor / firm bed. Put a resistance band around your study leg just above the knee and attach it to a secure object like a table leg or bed. Start with your study leg falling slightly out towards the pull of the band.	Squeezing the inside of the thigh on your study leg, bring the study leg into the midline against the pull of the resistance band. Hold for 3 seconds and then slowly return to the starting position.	Advanced options: 1. Change to a harder resistance band. 2. Add a bridge while holding your leg in the midline: squeeze your buttock muscles, tuck your tailbone under and lift your hips and buttocks from the floor. Then lower your buttocks down and return to the starting position.
Hip external rotator exercises	Lying leg rotations	Lie on your front on a firm surface with a resistance band around the ankle of your study leg. Attach the band to a secure object like a table leg or bed.	Bend the knee on your study leg to 90 degrees and allow the lower leg to fall out with the pull of the resistance band. Keep your thighs in the same position while you rotate the lower leg inward to the midline, pulling against the band. Hold for 3 seconds in this position. Control the leg as you rotate it back to the starting position.	Change to a harder resistance band as guided by your physiotherapist.
	Hip aeroplanes	Start standing in front of a bench, couch or bed, with your feet hip width apart.	Standing only on the study leg, left the other leg up behind you as you tip forward. Try and make your lifted leg and torso in a straight line horizontal to the ground. Only use your hands on the bench/couch/bed as you need to for support. Rotate your pelvis and upper body slowly away from the study leg by pushing through your study leg, and then slowly lower the pelvis to the starting position. Stand back upright, bringing both feet back to the ground.	Advanced options: 1. Complete the exercise without holding onto the bench/couch/bed for support. 2. Add a cuff weight to the non-study leg.
Balance exercises	Tandem stance	Stand on a firm surface. Look forwards focusing on a point on the wall. Use hand support (e.g. a chair) for balance if required.	Place 1 foot in front of the other so that feet make a straight line. Hold for 10 seconds. *“Hold, 2, 3, 4, 5, 6, 7, 8, 9, relax”.* Switch foot position so that the foot that was in front is now in the back. Hold for 10 seconds. *“Hold, 2, 3, 4, 5, 6, 7, 8, 9, relax”.*	1. Let go of hand support (if required) as you feel stable. 2. Maintain balance while slowly raising arms in the air. 3. Eyes closed.
	Forwards tap	Stand on a firm surface. Use hand support (e.g. a chair) for balance if required.	Slowly tap forwards and back with the ‘tapping leg’ (non-arthritis leg) while balancing on the arthritis leg. Start with tapping just a few inches forwards and backwards and progress to larger taps as you gain control. Keep your weight on the arthritis leg. Concentrate on keeping your knee positioned over your foot throughout.	
	Single leg balance	Stand with your feet shoulder width apart. Stand close to a wall for support in case you over balance, if required. Use hand support (e.g. a chair) for balance, if required.	Stand on single leg. Try to hold for 10 seconds. *“Lift, 2, 3, 4, 5, 6, 7, 8, 9, relax”.* Keep your weight on the arthritis leg. Concentrate on keeping your knee positioned over your foot throughout.	1. Increase hold time for up to 30 secs, as you feel stable. 2. Maintain balance while slowly raising and lowering your arms in the air. 3. Eyes closed.
